## Abstract

**Background:**

Artificial intelligence (AI)–based chatbots could help address some of the challenges patients face in acquiring information essential to their self-health management, including unreliable sources and overburdened health care professionals. Research to ensure the proper design, implementation, and uptake of chatbots is imperative. Inclusive digital health research and responsible AI integration into health care require active and sustained patient and stakeholder engagement, yet corresponding activities and guidance are limited for this purpose.

**Objective:**

In response, this manuscript presents a master protocol for the development, testing, and implementation of a chatbot family in partnership with stakeholders. This protocol aims to help efficiently translate an initial chatbot intervention (MARVIN) to multiple health domains and populations.

**Methods:**

The MARVIN chatbots study has an adaptive platform trial design consisting of multiple parallel individual chatbot substudies with four common objectives: (1) co-construct a tailored AI chatbot for a specific health care setting, (2) assess its usability with a small sample of participants, (3) measure implementation outcomes (usability, acceptability, appropriateness, adoption, and fidelity) within a large sample, and (4) evaluate the impact of patient and stakeholder partnerships on chatbot development. For objective 1, a needs assessment will be conducted within the setting, involving four 2-hour focus groups with 5 participants each. Then, a co-construction design committee will be formed with patient partners, health care professionals, and researchers who will participate in 6 workshops for chatbot development, testing, and improvement. For objective 2, a total of 30 participants will interact with the prototype for 3 weeks and assess its usability through a survey and 3 focus groups. Positive usability outcomes will lead to the initiation of objective 3, whereby the public will be able to access the chatbot for a 12-month real-world implementation study using web-based questionnaires to measure usability, acceptability, and appropriateness for 150 participants and meta-use data to inform adoption and fidelity. After each objective, for objective 4, focus groups will be conducted with the design committee to better understand their perspectives on the engagement process.

**Results:**

From July 2022 to October 2023, this master protocol led to four substudies conducted at the McGill University Health Centre or the Centre hospitalier de l’Université de Montréal (both in Montreal, Quebec, Canada): (1) MARVIN for HIV (large-scale implementation expected in mid-2024), (2) MARVIN-Pharma for community pharmacists providing HIV care (usability study planned for mid-2024), (3) MARVINA for breast cancer, and (4) MARVIN-CHAMP for pediatric infectious conditions (both in preparation, with development to begin in early 2024).

**Conclusions:**

This master protocol offers an approach to chatbot development in partnership with patients and health care professionals that includes a comprehensive assessment of implementation outcomes. It also contributes to best practice recommendations for patient and stakeholder engagement in digital health research.

**Trial Registration:**

ClinicalTrials.gov NCT05789901; https://classic.clinicaltrials.gov/ct2/show/NCT05789901

**International Registered Report Identifier (IRRID):**

PRR1-10.2196/54668

## Introduction

### Background

Self-management is key to patient health, and interventions to promote it are being increasingly implemented in the delivery of health care. Effective self-management involves multiple aspects, including problem-solving, decision-making, resource use, patient–health care professional partnership building, and taking action [1,2]. To improve self-management, patients often seek guidance from health care professionals, staff and volunteers from community organizations or peers, and a variety of internet resources [3,4]. However, the availability of these actors and resources can be inconsistent. Moreover, information encountered on the internet varies in quality [5-7]. From reliable but complex scientific articles to opinion blogs or outdated web pages, these sources do not always provide the clearest, most accurate, or most reassuring guidance. The importance of self-management has been further highlighted by the COVID-19 pandemic, which introduced additional barriers to accessing regular follow-up [8] and exposed individuals worldwide to an infodemic [9,10].

In addition to these challenges, frontline professionals are often confronted with complex questions from patients regarding treatment instructions, comorbidity management, side effects, and drug interactions. However, in the context of swiftly evolving knowledge and overwhelming workloads, health care professionals may not have sufficient expertise and time for certain questions [11,12]. Their responses may vary depending on their individual training, proficiency, and clinical experience. Rapidly obtaining accurate and clear health information and relaying it to patients can be a daunting challenge for professionals.

Safe and effective digital health interventions could help address the limitations of existing self-management or care support. A particularly promising avenue is the emergence of artificial intelligence (AI)–based chatbots—software applications that interact with users through simulated human text or voice conversations via smartphones or computers. Often harnessing AI to enable natural language interpretation and assist in decision-making, such tools possess the potential to revolutionize patient self-management and support [13]. They can be applied to diverse platforms to foster mutually beneficial outcomes for health systems and patients, including less time spent in hospitals, outpatient efficiency, and personalized treatment [9].

Successful implementation of an intervention (ie, positive implementation outcomes) is necessary to achieve desired changes in clinical or service outcomes [14]. Multiple studies have investigated the implementation of health-oriented chatbots, including in the areas of mental health support [15-17], problematic substance use treatment [18], cirrhosis patient education [19], and asthma self-management [20]. Nevertheless, such studies have typically focused on feasibility and usability in small-scale prototype implementations [21-23]. Digital health products are often dealt with through an “implement now, clinically validate later” ethos [24], as they encompass a large number of different technologies. Thus, there is no clear consensus on methods for assessing the clinical effectiveness of digital health interventions [24], and data on the impact of chatbot interventions on clinical outcomes are scarce [25]. Large user samples are necessary to gain more robust insights into chatbot implementation. In-depth studies including other valuable implementation (eg, fidelity, appropriateness, sustainability, and cost-effectiveness) and clinical (eg, safety, effectiveness, and efficacy) outcomes will also be critical for scaling up and long-term adoption of chatbot interventions.

Finally, very little engagement of stakeholders, including patients and health care professionals, has led to poor usability and low adoption of many digital health interventions [26]. In the context of chatbot development, a scoping review investigating patient engagement revealed limited involvement of patients and insufficient reporting of the relevant activities [27]. Among the 16 studies included, only 8 mentioned patient engagement, with just 3 offering adequate details on the methods and approach used. The authors also pointed out that future chatbot development would need to integrate multifaceted means of patient participation and document them thoroughly. Stakeholders should be engaged in defining research objectives and designing interventions tailored to their needs [28]. According to the patient-public partnership continuum proposed by the Montreal model [29], this inclusivity can be extended to “co-construction,” where patients and stakeholders are involved throughout the process. Meanwhile, to answer the many questions raised by the use of intelligent machines and ensure that AI develops in harmony with democracy, the responsible integration of AI necessitates a co-construction process [30]. Engaging end users in discussions about the challenges posed by AI and drawing on their lived experiences can reveal key aspects of digital health research that might otherwise be overlooked [31], thus better paving the way for success.

Since 2020, led by YM, SA, and [name], an innovative chatbot named *Minimal AntiRetroViral INterference* (now named *MARVIN*) has been in development for people with HIV. Through a co-design approach involving patients and stakeholders, MARVIN aims to facilitate antiretroviral therapy self-management. The authors’ team subsequently trialed the MARVIN chatbot among people with HIV and validated its usability and acceptability [32]. Given the initial success of MARVIN among people with HIV, we intend to build on this pilot study to increase MARVIN’s areas of specialization and continue to develop our algorithms to improve MARVIN’s intelligence, thereby expanding its reach and potential benefits to a broader audience.

### Aim and Objectives

Grounded in patient and stakeholder engagement strategies and implementation science, this protocol aims to describe the methods and tools necessary to efficiently develop the innovative MARVIN chatbot interventions across multiple health domains and populations and assess their implementation for robust and widespread use. The study’s primary objectives are to co-construct versions of MARVIN adapted for different health conditions and target populations (objective 1: development), assess their global usability (usability and acceptability) in a small participant sample context (objective 2: usability), and measure implementation outcomes (usability, acceptability, appropriateness, adoption, and fidelity) in the context of a large sample (objective 3: implementation) through a mixed methods approach in the respective setting of each chatbot. The secondary objective is to evaluate the impact of different stakeholder partnerships established for the aforementioned objectives on the development of the AI health care chatbots (objective 4: partnership evaluation).

## Methods

### Study Design

This multicenter study follows the CONSORT (Consolidated Standards of Reporting Trials) extension for pilot and feasibility trials [33], CONSORT-EHEALTH (Consolidated Standards of Reporting Trials of Electronic and Mobile Health Applications and Online Telehealth) [34], and CONSORT-AI (Consolidated Standards of Reporting Trials–Artificial Intelligence) [35] guidelines (Multimedia Appendices 1-3 [33]), as well as the Montréal Declaration for a Responsible Development of Artificial Intelligence [30] regarding the ethical conduct of research involving humans and AI.

The study is presented in the form of a master protocol, defined as a single overarching design developed to evaluate multiple hypotheses with the overall goal of increasing efficiency and establishing uniformity through the standardization of procedures in the development and evaluation of different interventions [36]. This master protocol will encompass multiple parallel individual chatbot projects sharing the MARVIN chatbot technology, subsequently referred to as “substudies.” The chatbot of each substudy is considered as a distinct intervention as it will integrate specific features or content tailored to the corresponding health care setting (health condition and target population). The chatbots will be implemented in these different populations without control groups.

To accommodate this, we used an adaptive platform trial design, which combines features of both basket trials (designed to test a single intervention in different populations) and platform trials (designed to test multiple interventions in the context of a single disease) [37]. As defined by the US Food and Drug Administration, an adaptive platform design is appropriate for our trial as it allows for flexibility in managing multiple interventions adapted to different populations while enabling the early removal of ineffective interventions and introduction of new interventions based on interim data [38].

As shown in the example in Figure 1, substudy arms targeting different conditions can be initiated at different time points. The substudies are independent of each other, and their processes are illustrated in Figure 2. Objectives 1 to 3 will be completed in a sequential manner, whereas objective 4 will be assessed throughout the process. A decision will be made on whether to continue with the same chatbot intervention version in objective 3 (implementation) based on the results of objective 2 (usability). In addition, there is no initial fixed duration or sample size for each substudy.

This master protocol outlines the common elements of the individual chatbot substudies in terms of objectives and processes. Concurrently, each substudy will have its own subprotocol describing more specific standardized operational structures; additional inclusion and exclusion criteria; recruitment and selection methods; and data collection, analysis, and management. All subprotocols will be managed as appendices to this master protocol and will be subject to further review by the research ethics board (REB) when they are ready. In addition, certain criteria of the master protocol may be redefined by the research team based on progress in each substudy and submitted as amendments to the REB for review for subsequent application to all substudies.

**Figure 1 figure1:**
[figure not shown]
Adaptive platform trial design without control group.

**Figure 2 figure2:**
[figure not shown]
Study steps for each substudy.

### Ethical Considerations

This study received approval from the McGill University Health Centre (MUHC) REB on August 9, 2023 (approval MP-37-2023-9333); the Centre hospitalier de l’Université de Montréal REB (approval MEO-37-2024-11732) on October 13, 2023; and the Polytechnique Montréal REB (approval CER-2324-29-D) on October 10, 2023. It is also registered in the ClinicalTrials.gov database (NCT05789901).

### Settings and Participants

This study will be conducted at the MUHC and the Centre hospitalier de l’Université de Montréal, both located in Montreal, Quebec, Canada. The study participants include patients and health care professionals, who will be the end users of the chatbots.

### Eligibility Criteria

The primary inclusion criteria for participants are as follows: (1) age of ≥18 years; (2) fluency in English or French; (3) ability to understand the requirements of study participation and provide oral and written informed consent before and during the implementation of the study; (4) access to a smartphone, tablet, or computer in a private environment; and (5) access to an internet connection or data plan on their device. Specific to objectives 2 (usability) and 3 (implementation), additional inclusion criteria are (6) acceptance of using or creating a personal Facebook (Meta Platforms) account, (7) acceptance of using a Facebook Messenger-based chatbot, and (8) acceptance of Facebook’s privacy and data security policies.

Participants may not take part if they (1) are affected by a cognitive deficit or medical instability that prevents them from participating in any aspect of the study and (2) self-report being insufficiently able to use the chatbot with the technical support provided. For objectives 2 (usability) and 3 (implementation), the patient partners involved in the co-construction design committee (defined in the following section) will not be able to participate in either phase.

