### Recruitment and Sample Size Justification

Objectives 1, 2, and 3 will use convenience sampling to recruit participants through different channels, including clinics, patient foundations, community-based organizations, and professional associations [39]. For example, patient participants will be introduced to the study by their health care service provider (eg, physician, nurse, or social and community worker) during their visits. Informational materials such as study flyers and a video (Multimedia Appendix 4) showcasing the MARVIN chatbot will be disseminated via email, newsletters, or a website.

Participants will be required to consent before engaging in each objective. For objectives 1 (development) and 2 (usability), interested individuals can reach out to the study coordinator. Detailed study procedures, eligibility checks, and consent collection will be facilitated by the study coordinator for those expressing interest. Verbal consent may be adopted for participants who continue from objective 1 to objective 2. This will be obtained remotely through teleconference with an impartial witness to ensure compliance with all aspects of free and informed consent. Following the co-construction approach [30], a co-construction design committee consisting of researchers, health care professionals, and volunteer patient partners will be formed starting from objective 1 to carry out the subsequent development. The sample size for objective 1 is 20 participants to ensure saturation for the needs assessment focus groups [40], whereas 30 participants will be recruited to complete the corresponding usability test for objective 2. This sample size is common for pilot studies and satisfies the minimum size recommended in the literature [41,42].

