For objective 3 (implementation), an optimized version of the chatbot will be accessible from the web around the clock, 7 days a week, for translational research. As currently the MARVIN chatbots will be only released in Canada, recruitment will be exclusive to the Canadian population, and participants will engage in an electronic consent process through the MARVIN chatbots. Before using the chatbot, individuals will be required to review and accept MARVIN’s privacy policy (Multimedia Appendix 5). Subsequently, they will be asked to review an electronic version of the information and consent form and then answer the following verification questions for eligibility criteria 1 to 3 via the chatbot: (1) *Are you at least 18 years old?* (2) *Are you comfortable using English or French while communicating with the chatbot?* (3) *Do you agree to participate in the study as described above?* The remaining criteria (4 to 8) will be met once users connect to the chatbot. Should participants agree to participate, their responses will be securely recorded in a separate encrypted database on the MARVIN cloud servers and synchronized to the electronic enrollment log. If users opt not to participate, no records will be kept. As a Facebook account will be a prerequisite for using the chatbot, no further measures will be taken to detect or prevent the possibility of multiple identities. The target sample size of 30 to 150 participants was obtained based on the usability, acceptability, and appropriateness outcomes, which are considered key outcomes for this objective. The analysis involves a 1-sided Student *t* test (1-tailed) evaluating whether the corresponding average attains a predetermined threshold. A power analysis for a 1-sample *t* test is then performed, with 80% power and a 5% significance level. Within the targeted sample size (30≤n≤150), small to moderate standardized effect sizes (0.2≤Cohen *d*≤0.5) are detectable in the total sample with the aforementioned statistical power.

Regarding objective 4 (partnership evaluation), upon completion of each objective, an email invitation will be sent to organize focus groups with stakeholders involved in the chatbot co-construction design committee.

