It is possible that the MARVIN chatbots will have difficulty understanding messages from participants during the study. In such instances, the chatbot will indicate that it cannot understand, as described previously in Figure 5, and suggest seeking help from a health care professional. There is also a small chance that the chatbot will provide erroneous advice. As an example, the chatbot might inform a patient who missed a 2-hour dose to stop taking the medication completely and consult a health care professional immediately. To minimize this potential risk, participants will be informed of the limitations of the chatbots during the consent process. In addition, participants will be prompted to report any perceived inaccuracies and their consequences to the research team in a timely manner. Weekly revisions of user chat logs will be conducted by the research team to ensure timely human intervention in the event of errors. The governance board for this study will consistently monitor and discuss these reports.

Finally, any other service-related risks (eg, chatbot or Facebook network service disruptions) will be communicated to each participant in a timely manner and properly documented by the study coordinator.

Participation in the study presents benefits, including early access to chatbot interventions with validated health care information. Participants will also be compensated appropriately upon completion of each study objective [74] in the form of a gift card or, exceptionally, a money transfer.

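### The bar on co-designers in Objectives 2 and 3 covers patient partners only, and the Objective 3 chatbot screen leaves the protocol's own exclusions, committee bar and Canada-only rule unapplied

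*Protocol article*

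**What the plan says.** All places are in the Methods of the protocol article.

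- **Who builds the chatbot.** Under Recruitment and Sample Size Justification, "a co-construction design committee consisting of researchers, health care professionals, and volunteer patient partners will be formed starting from objective 1".
- **Who may rate it.** Under Settings and Participants, "The study participants include patients and health care professionals, who will be the end users of the chatbots".
- **Who is kept out of Objectives 2 and 3.** Under Eligibility Criteria, "the patient partners involved in the co-construction design committee (defined in the following section) will not be able to participate in either phase". No other committee member is mentioned.
- **How Objective 3 users are screened.** The chatbot puts three questions (age, comfort in English or French, agreement to take part), which stand for inclusion criteria 1 to 3. For the other inclusion criteria, "The remaining criteria (4 to 8) will be met once users connect to the chatbot".
- **Residence.** "recruitment will be exclusive to the Canadian population", with release of the chatbots only in Canada given as the reason.
- **Duplicates.** Because a Facebook account is required, "no further measures will be taken to detect or prevent the possibility of multiple identities". Inclusion criterion 6 accepts an account created for the purpose.
- **Compensation.** Under Anticipated Risks and Benefits, "Participants will also be compensated appropriately upon completion of each study objective", normally as a gift card.

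**The concern.** The sponsor saw that people who helped to design a chatbot should not be the ones who score it, and closed that route for patients only. Professionals on the committee have the same interest in the product and belong to a group that may enrol. Their scores would enter one-sample tests against fixed thresholds (68/100 on the UMUX-Lite and 24/30 on the AES in Objective 2, with appropriateness thresholds added in Objective 3). There is no control group in which such a bias could cancel. Objective 2 results also decide whether the same chatbot version goes on to implementation, so an upward bias there helps a version through.

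The Objective 3 screen raises a second, smaller issue. The protocol sets two exclusions, a committee bar and a restriction to Canada, and the screen that enrols people asks about none of them. Repeat entries by one person would also break the independence that the t test assumes, and the plan has no means of seeing them.

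**Working it through.** **1. Side-by-side reading.**

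| Rule in the protocol | Applied by the Objective 3 screen? |
|---|---|
| Inclusion 1 to 3 (age, language, consent) | Yes, three questions |
| Inclusion 4 to 8 (device, connection, Facebook terms) | Taken as met on connection |
| Exclusion 1 (cognitive deficit or medical instability) | Not asked |
| Exclusion 2 (unable to use the chatbot) | Not asked, though getting through the dialogue is a partial screen |
| Patient partners on the committee barred | Not asked |
| Professionals on the committee barred | No such rule |
| Canadian population only | Not asked, and no technical check described |
| One record per person | Expressly not checked |

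In Objective 2 the study coordinator handles eligibility checks. That deals with ineligible and repeat users there. It cannot remove professional co-designers, because no criterion excludes them.

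**2. The plan's own figure.** Inputs: n = 30 to 150, 80% power, 5% level, one-sided one-sample t test, stated detectable d of 0.2 to 0.5. Exact noncentral-t power gives a smallest detectable d of 0.465 at n = 30 and 0.204 at n = 150. The stated range therefore reproduces to one decimal and is not in dispute.

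**3. Co-designers among the raters (illustration).** The article gives neither the number who might enrol nor how they would score. Assume that k of n raters score δ SD above the rest and that everyone else's mean lies exactly on the threshold. With f = k/n, the sample mean is shifted by fδ and the SD becomes √(1 + f(1−f)δ²). For k = 2, n = 30, δ = 0.5, the shift is (2/30) × 0.5 = 0.033 SD. False-success rates at a nominal 5%:

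| n | k | δ = 0.5 SD | δ = 1.0 SD |
|---|---|---|---|
| 30 | 2 | 7.1% | 9.7% |
| 30 | 5 | 11.4% | 20.9% |
| 150 | 5 | 7.5% | 10.7% |
| 150 | 10 | 10.7% | 19.6% |

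**4. Repeat records (illustration).** Assume that m of n records are exact second copies of another participant's record. The variance of the mean is then inflated by (4m + (n − 2m))/n relative to n independent records.

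- n = 150, m = 30 (20%): (120 + 90)/150 = 1.40. Effective n = 150/1.40 = 107. The true standard error is √1.40 = 1.18 times the naive one, so the naive one is 1 − 1/1.18 = about 15% too small. One-sided alpha is about 8.1%.
- n = 150, m = 15 (10%): (60 + 120)/150 = 1.20. Alpha is about 6.5%.
- n = 150, m = 8 (about 5%): (32 + 134)/150 = 1.107. Alpha is about 5.8%.

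At modest rates, repeats matter little. A few favourable co-designers in a sample of 30 matter more.

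**The case against.** The strongest reply is that much of this may be settled in documents that are not shown. Study Design leaves additional eligibility criteria and selection methods to each subprotocol. The consent form, which users review before agreeing, may state the exclusions and the residence rule. Release only in Canada may limit access in practice. The HIV and breast cancer chatbots are described for patients, so a committee clinician is not an obvious rater there. The Discussion admits that self-referral makes the inclusion criteria hard to assess, and promises outlier checks. Compensation follows completion of an objective that is expected to last 12 months, which weakens any motive to enrol twice.

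Part of this stands. It narrows the professional co-designer gap mainly to chatbots for professionals, and it makes the duplicate point minor. It does not remove either one. The article words the committee bar, lists the screening questions and declines duplicate checks as rules common to all substudies, so these are stated choices and not details lost in condensing. Outlier checks would not reveal plausible favourable scores or a second account.

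Two stronger readings are tempting. A reader might infer that Objective 3 fails to confirm membership of the target population. The documents do not support that: additional criteria are delegated to the subprotocols, and deployment is meant for the general population. A reader might also infer that nothing at entry shows whether a patient or a professional appropriateness instrument applies. Participants receive a sociodemographic questionnaire at entry, and its content is in an appendix that is not shown, so this cannot be judged.

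**Conclusion.** The point holds in two parts of unequal weight. The firm part is the committee bar: as written, health care professionals who co-designed a chatbot may take part in the threshold tests of Objectives 2 and 3, most clearly in MARVIN-Pharma. If they score favourably, the bias is upward. The lesser part is the Objective 3 screen, which does not apply the protocol's own exclusions, committee bar or Canada-only restriction and leaves repeat entries unseen. The protocol discloses some of this.

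The size is unknown. The error rates above rest on assumed numbers of co-designers, an assumed score advantage and identical repeat records. They show what could happen, not what is expected. Nothing in the article shows that co-designers will enrol or that duplicates will be common. The change is worth making because it is cheap and enforces rules that the sponsor already wrote. The design and the sample size are not called into question.

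**What to change.** 1. In Eligibility Criteria, extend the bar from patient partners to every member of the co-construction design committee, for Objectives 2 and 3.
2. Add three yes/no items to the Objective 3 chatbot consent: lives in Canada; neither exclusion applies; not a member of the design committee. Self-report does not verify these, but it puts each rule to the user and records the answer.
3. Flag suspected duplicates, for example from the Facebook account names already collected or when compensation is issued. Report the usability, acceptability and appropriateness tests again with one record per person, as a sensitivity analysis. Do not delete records automatically on matching sociodemographic answers, since distinct people can match. A check on the payee would need identity data that the Data Management, Confidentiality, and Security section does not describe collecting for Objective 3, so it should be used only if issuing compensation already yields such data.

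Cost: a slightly longer consent dialogue, a few lost raters, and an amendment to the research ethics board, which Study Design already foresees for changes to the master protocol's criteria.
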